##### **Confounding variables**

Randomized trials can be expensive, resource intensive to perform, and in certain circumstances unethical to perform; i.e., it might be difficult to ask (and trust) a large group of patients suffering from chronic inflammatory diseases to change their diet significantly (LFHM → HFLM, and vice versa). For these reasons, the BELIEVE study group have to rely on observational data. The challenge with observational data is that group allocation are not applied randomly, likely leading to selection bias with some corresponding confounding variables. In well performed Randomized Controlled Trials there will be no selection bias when splitting participants up into the control (e.g., LFHM) and treatment (e.g., HFLM) groups; it accounts for all possible “confounding variables” [48].

Improved confounding variable balance between exposure (HFLM) and control (LFHM) groups can be achieved by adjusting observations from each group based on the propensity score, which in this case would be the probability (1/3) that a patient received the experimental intervention (HFLM) given the observed covariates. Propensity score analysis seeks to isolate the treatment as the only difference between our treatment and control groups. Thus, propensity score methods attempt to correct for the assignment mechanism by providing a “balancing variable that creates” control units similar to treatment units at baseline (i.e.  $Y_{0|HFLM} \approx Y_{0|LFHM}$ ).

Confounding variables are independent variables other than the treatment variable (LFHM and HFLM, respectively) that are correlated to the outcome of the study. In order to identify possible confounders and develop propensity scores, we will use the following pragmatic definition (illustrated below) of what potentially makes a confounding variable (C):

- The Covariate (C) is an ancestor (cause) of the outcome (Y)
- The Covariate (C) probably cause the exposure (X; e.g., group)
- The Covariate (C) is not a descendant (effect) of the exposure (X) or outcome (Y)

[figure not shown]

Variables we will test for possible confounding of the association between dietary profile and treatment response is sex, age, and smoking status [14, 15, 49, 50]. Other adjusting variables include CID type and clinical center.

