### 3.2. Sample size and power considerations

Deciding on sample size is a well-known difficulty with exploratory prognostic factor research studies. To obtain an adequate number of outcome events, we applied 'the rule of thumb', whereby 10 outcomes are needed for

each independent variable. We planned to enroll 320 patients in total with the anticipation that 50% of these would experience a clinical response within the 14–16 weeks period after initiation of biological therapy. With this in mind and anticipating that we would observe at least 160 events (i.e., clinical response among the 320 patients), the study would be sufficiently powered to explore the impact of as many as 16 independent variables including condition and clinical center. Since using the ‘rule of thumb’ method to justify sample size is a debated practice, we went one step further and estimated the statistical power to detect differences between two dietary groups. For the contrast between groups and for a comparison of two independent binomial proportions (those with high-fiber, low-meat intake vs. other) using Pearson’s  $\chi^2$  statistic, with a  $\chi^2$  approximation, with a two-sided significance level of 0.05 ( $P < 0.05$ ), a total sample size of 318—assuming an ‘allocation ratio’ of 1 to 2 (one-third)—has an approximate power of 0.924 (i.e., >90% statistical power) if the anticipated proportions responding to therapy are 60% and 40%, respectively. However, due to pre-specified time constraints, inclusion to BELIEVE was terminated on 03-30-2020 before reaching the planned sample size of 320 patients in total.

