### **SAP modifications:**

- 1) There were no patients with Hidradenitis Suppurativa and Non-infectious Uveitis included in the study.
- 2) Patients initiating all kinds of biological therapy were enrolled instead of only TNFi therapy\*.
- 3) In addition, patients that previously have received biologic treatment were also made eligible\*.

*\*We will apply these new strata in subsequent sensitivity analyses*

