## 6. Analysis

### 6.1. Outcome definitions, measurement and calculation

#### 6.1.1. Primary outcomes

The primary endpoint [2] is the proportion of patients with a clinical response to therapy 14-16 weeks after initiation of treatment with a biological agent. Thus, the primary outcome will be a composite depending on the disease specific definitions of clinical response, defined below:

- CD/Crohn's disease: clinical remission, defined as Harvey-Bradshaw Index (HBI) of 4 or less [25].
- UC/Ulcerative colitis: clinical remission, defined as Mayo Clinic Score of 2 or less (with no individual subscore of >1) [26-28].
- RA/Rheumatoid arthritis: clinical response, defined as at least a 20% improvement according to the criteria of the American College of Rheumatology (ACR20) [29, 30].
- AxSpA/Axial spondyloarthritis: clinical response, defined as at least a 20% improvement according to the Assessment of Spondyloarthritis International Society (ASAS20) [31, 32].
- PsA/Psoriatic arthritis: clinical response, defined as at least a 20% improvement according to the criteria of ACR20 [33].
- PsO/Psoriasis: clinical response, defined as at least a 75% improvement in the Psoriasis Area and Severity Index (PASI 75) [34].

For the measurement and calculation of HBI, Mayo Clinic Score and PASI see table A. ACR20 and ASAS20 are composite outcome measures defined below with composites further explained in table A.

ACR20 is a composite measure developed by the American College of Rheumatology for assessment of improvement of RA patients in clinical trials [30] but also used for assessment of PsA [33]. ACR20 is defined as  $\geq 20\%$  improvement in tender and swollen joint counts and  $\geq 20\%$  improvement in at least three out of the following five measures: 1) pain, 2) patient global assessment, 3) physician global assessment, 4) self-assessed

physical disability and 5) CRP or erythrocyte sedimentation rate. Information for calculation of ACR20 will be extracted from the Simplified Disease Activity Index (SDAI; patients and physicians global assessment and tender and swollen joint count) and the Health Assessment Questionnaire Disability Index (HAQ-DI; disability, see table A), while pain is a separate question in the self-administered questionnaire ("how much pain due to your arthritis do you suffer from, the past two days?") on a VAS 0-100 mm.

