#### 6.1.4. Exposure and confounding variables

##### **Exposure variable**

We will stratify the patients in BELIEVE into two groups (exposed versus unexposed) based on the ratio of fiber to meat intake (FtM [grams per day]):

$$FtM = \frac{\text{Fibers}}{\text{Red and processed meat}},$$

which will be calculated from the food frequency questionnaire (FFQ) administered to the patients at baseline. From this ratio, exposure is defined as the upper 33.3% of the total study sample (called the high fiber low meat group, HFLM) leaving the lower 66.6% of the sample as those un-exposed (low fiber high meat, LFHM).

Secondary explorative analysis will include defining exposure as 1) the upper 33.3% (high fiber; HF) of the study sample with respect to intake of dietary fibers (versus the lower 66.6% [low fiber; LF], and 2) the lower 33.3% (low meat; LM) of the study sample with regard to red/processed meat intake (versus the upper 66.6% [high meat; HM]).

The FFQ used in the present study was developed and validated in relation to the 2007-2008 Danish Health Examination Survey [47]. It was internet-based and administered to the participants prior to initiation of biological therapy with questions covering the habitual dietary intake during the past month. The FFQ contained information from 267 different food groups. For each item, frequency of consumption was evaluated by eight categories ranging from “newer/seldom” to “twice or more per day”. In order to quantify portion sizes for main meals and other main food items, a photographic food atlas consisting of different food and meal series was included at the end of the questionnaire. However, fixed portion sizes were used for some food items with more standardized portion sizes such as fruits. The actual weight in grams for each food item will be derived by multiplying the reported frequency of consumption with estimated portion sizes. Total energy intake and intake of different nutrients will be quantified using the Danish Food Composition Tables (National Food Institute, Technical University of Denmark, <https://frida.fooddata.dk/>).

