## 6.2. Analysis methods

The baseline characteristics of the participants (table 1) will be summarized for each dietary exposure profile (HFLM and LFHM) using descriptive statistics. Data will be presented as either means and standard deviations (SDs), or medians and interquartile ranges (IQRs) for continuous outcomes, and numbers and percentages for binary outcomes.

The primary outcome is the proportion of patients with a clinical response to therapy 14-16 weeks after treatment initiation. Response is defined for each CID (see section 6.1.1.). The number and proportion of participants who achieved treatment response will be summarized based on dietary profile (fig. 2 and table 2). We will investigate the association between dietary profile at baseline (HFLM and LFHM) and treatment response (yes/no) on the ITT population using logistic regression models. A simple (unadjusted) logistic regression model, an adjusted model (adjusted for type of CID, clinical center, age, sex, smoking) and a propensity adjusted model (further adjusted for propensity score) will be presented in table 2. The Odds ratio (OR) of achieving clinical response at week 14-16 for CID patients in HFLM group (the upper 33.3 % of the study population based on the ratio of fiber to meat intake) versus the LFHM group (the lower 66.6 %) will be reported along with the 95 % confidence interval (CI) and two-sided p-value (fig. 2 and table 2). We will also perform similar analyses on the key secondary outcome measures (see 6.1.2.), corresponding to our pre-specified key secondary objectives.

Secondary explorative analyses will include repeating the logistic regression models for treatment outcomes using secondary predictors of interest; 1) the upper 33.3% (high fiber; HF) vs. the lower 66.6% (low fiber; LF) of the study sample with respect to intake of dietary fibers (adjusted for meat intake), and 2) the lower 33.3% (low meat; LM) vs. the upper 66.6% (high meat; HM) of the study sample with regard to red/processed meat intake (adjusted for fiber intake). In addition, a possible interaction between the lower 33.3% of the sample

with respect to red/processed meat intake and the upper 33.3% of the sample with regard to fiber intake will be examined using logistic regression with same covariates as stated above.

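### No covariate list commits to baseline disease activity or to the baseline value of a change score, although CD and UC response are absolute thresholds

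*SAP*

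**What the plan says.** The confounding part of section 6.1.4 states: "Variables we will test for possible confounding of the association between dietary profile and treatment response is sex, age, and smoking status". It then adds CID type and clinical centre as adjusting variables.

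Section 6.2 and the Table 2 footnotes fix three models: a crude one (adjusted for CID type, according to the footnote), one with CID type, centre, age, sex and smoking, and the same with a propensity score added. Appendix Tables 3 and 4 add only meat or fibre intake. The Appendix Table 2 note says the sensitivity analyses take the same adjustment as the primary analysis.

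In section 6.1.1, CD response is "clinical remission, defined as Harvey-Bradshaw Index (HBI) of 4 or less". UC response is a Mayo score of 2 or less, or a partial Mayo of 1 or less where endoscopy is missing (section 4.2). RA, axSpA, PsA and PsO use improvement from baseline. Section 5.2.1 requires a diagnosis and the start of a biologic, and no minimum activity.

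The FFQ was completed before the biologic, with "questions covering the habitual dietary intake during the past month".

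Nine of the ten key secondary outcomes in section 6.1.2 are changes from baseline. Their analysis is given in one sentence of section 6.2: "We will also perform similar analyses on the key secondary outcome measures".

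**The concern.** Section 6.1.4 treats a covariate as a confounder if it causes the outcome, probably causes the exposure, and is not an effect of either.

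- **Outcome.** In CD and UC, baseline activity meets the first condition almost by construction. A CD patient who enters at HBI 4 or below and stays there counts as a responder.
- **Exposure.** HBI and Mayo score stools, bleeding and abdominal pain. Such symptoms in the month before the biologic may have shaped the fibre intake that the FFQ recorded.

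If the high-fibre, low-meat group (HFLM) and the comparison group (LFHM) differ in baseline activity, part of any difference in response reflects that imbalance. The sensitivity analyses would not reveal it, because they use the same covariates.

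For change scores the issue is a standard one. A baseline imbalance alone produces a difference in change through regression to the mean, and leaving out the baseline value loses precision. P values from these models feed the multiplicity procedure of section 4.1, so the model should be fixed in advance.

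**Working it through.** **The plan's own figure.** Section 3.2 gives "a total sample size of 318", a 1:2 split (106 and 212), 60% against 40% response, and a power of 0.924, "with a two-sided significance level of 0.05". Pooled response is (106×0.6 + 212×0.4)/318 = 0.4667. Then z = [0.20 − 1.96·√(0.4667×0.5333×(1/106 + 1/212))] / √(0.24/106 + 0.24/212) = 1.436, so power is 0.924. The figure reproduces and is not in dispute. The group sizes are used below; the final N fell short of 320 and is not stated.

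**Does another route commit to the adjustment?**
- The Table 1 footnote has variables with an SMD above 0.5 evaluated as potential confounders. At 106/212 the standard error of an SMD is √(1/106 + 1/212) = 0.119. An imbalance of 1.96×0.119 = 0.23 is already significant at 5%, while the trigger lies at 0.5/0.119 = 4.2 standard errors. Table 1 lists CRP, physician and patient global assessment, SF-12 and SHS, but not HBI, Mayo, SDAI, BASDAI or PASI.
- The propensity score conditions on observed covariates that are not listed. If these are the five named variables, the score adds almost nothing to a model that already contains them.

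**Primary outcome.** Assumptions, none from the SAP: log OR 0.7 per SD of baseline activity (about a factor of 2), HFLM less severe by 0.3 or 0.4 SD, 50% overall response, no diet effect. Averaging the logistic response over a normal activity score in each group gives:

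| SMD | Response HFLM / LFHM | OR, all affected | OR, 50% affected | OR, 31% affected |
|---|---|---|---|---|
| 0.3 | 53.1% / 48.4% | 1.21 | 1.10 | 1.06 |
| 0.4 | 54.2% / 47.9% | 1.29 | 1.13 | 1.08 |

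The last two columns stratify by disease and let activity act only in the IBD share s, so the pooled log OR is about s × log OR. For example, exp(0.31 × ln 1.21) = 1.06. The 31% is the planned 100 IBD patients of 320 (section 4.2); the actual share is not given. In percentage points, the gap is about 1.5 to 1.9 at 31%, 2.4 to 3.2 at 50% and 4.7 to 6.3 if all are affected, against the planned 20.

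**Change scores.** With baseline/follow-up correlation ρ and equal SDs, the spurious difference is (1 − ρ) × SMD. The residual variance with baseline in the model, relative to the plain change score, is (1 − ρ²)/(2 − 2ρ) = (1 + ρ)/2. For an assumed 0.3 SD gap:

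| ρ | Spurious difference | SF-12 points (SD 10) | Variance ratio |
|---|---|---|---|
| 0.3 | 0.21 SD | 2.1 | 0.65 |
| 0.5 | 0.15 SD | 1.5 | 0.75 |
| 0.7 | 0.09 SD | 0.9 | 0.85 |

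**Parameter budget.** The adjusted model has 1 (diet) + 5 (CID) + 5 to 7 (six hospitals or eight departments) + 1 (age) + 1 (sex) + 3 (smoking) = 16 to 18 terms. Section 3.2 allows 16 for 160 events.

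**The case against.** Several points on the other side stand.

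- **A model could still include severity.** A reader might infer that no planned model can adjust for it. The text does not show that: the propensity covariates are left open, and the SMD footnote could admit CRP or physician global assessment. What is missing is a commitment.
- **Activity may be an effect of diet.** The third criterion in section 6.1.4 excludes effects of the exposure. The FFQ records habitual intake, and the study hypothesis is that diet matters for disease, so baseline activity may partly follow from earlier diet. Adjustment could then remove part of the association of interest. The omission is therefore not plainly wrong on the SAP's own rule, but the choice needs to be stated.
- **Active disease at the FFQ is an inference.** The SAP says only that the questionnaire preceded the biologic and covered the past month.
- **The absolute threshold concerns CD and UC only.** Applying the bias to every patient gives the upper row of possibilities. In the other four diseases the direction is not established; ASAS20, for instance, needs an absolute gain of at least 10 units, which may be harder to reach from a low baseline.
- **Logistic regression on continuous outcomes is not intended.** Table 2 has a difference column and change rows, so the gap is one of wording.
- **Previous biologics and agent class are not ignored.** The SAP says "We will apply these new strata in subsequent sensitivity analyses", and the fourth sensitivity analysis in section 6.4 restricts to biologic-naive patients starting a TNF inhibitor.

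None of this supplies the baseline value for the change scores or a stated decision on baseline activity.

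**Conclusion.** The gap is real and of moderate size. Followed as written, the plan gives less precise and possibly biased estimates, most clearly for the primary outcome in CD and UC and for the nine change scores.

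The sizes in the tables are illustrations, because the SAP supplies no severity effect, imbalance or correlation. With the planned IBD share, the spurious OR is 1.06 to 1.08, small beside the planned contrast. The 1.21 to 1.29 requires activity to act equally in all six diseases.

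A reader might conclude that the omission biases the results towards the hypothesis. The documents do not support that. In CD and UC it would do so if HFLM patients were less severe. In the other diseases the sign is unknown. For change scores, less severe HFLM patients would show less improvement, which works against the hypothesis.

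This should be fixed, but it does not invalidate the plan.

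**What to change.** 1. In section 6.2, state that each continuous key secondary outcome is analysed by linear regression including the baseline value of the same measure, with the other covariates unchanged.
2. Add one baseline activity term to the adjusted model and to the propensity score: either a score standardised within each CID (HBI, Mayo or partial Mayo, SDAI, BASDAI, PASI) or the baseline physician global assessment. List the propensity covariates explicitly.
3. Report the current covariate set alongside, and say in section 6.1.4 that activity may be partly an effect of earlier diet, so that the two results can be read together.

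The cost is SAP wording and about one degree of freedom per model; the measures are already collected. Adjustment may remove an effect of earlier diet that acts through activity, which the model reported alongside would show. Terms for previous biologics, agent class and energy intake need not be part of this change: sensitivity analysis 4 covers the first two, no defect has been shown for the third, and the adjusted model is already at or above the 16-variable limit.

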## 6.2. Analysis methods

The baseline characteristics of the participants (table 1) will be summarized for each dietary exposure profile (HFLM and LFHM) using descriptive statistics. Data will be presented as either means and standard deviations (SDs), or medians and interquartile ranges (IQRs) for continuous outcomes, and numbers and percentages for binary outcomes.

The primary outcome is the proportion of patients with a clinical response to therapy 14-16 weeks after treatment initiation. Response is defined for each CID (see section 6.1.1.). The number and proportion of participants who achieved treatment response will be summarized based on dietary profile (fig. 2 and table 2). We will investigate the association between dietary profile at baseline (HFLM and LFHM) and treatment response (yes/no) on the ITT population using logistic regression models. A simple (unadjusted) logistic regression model, an adjusted model (adjusted for type of CID, clinical center, age, sex, smoking) and a propensity adjusted model (further adjusted for propensity score) will be presented in table 2. The Odds ratio (OR) of achieving clinical response at week 14-16 for CID patients in HFLM group (the upper 33.3 % of the study population based on the ratio of fiber to meat intake) versus the LFHM group (the lower 66.6 %) will be reported along with the 95 % confidence interval (CI) and two-sided p-value (fig. 2 and table 2). We will also perform similar analyses on the key secondary outcome measures (see 6.1.2.), corresponding to our pre-specified key secondary objectives.

Secondary explorative analyses will include repeating the logistic regression models for treatment outcomes using secondary predictors of interest; 1) the upper 33.3% (high fiber; HF) vs. the lower 66.6% (low fiber; LF) of the study sample with respect to intake of dietary fibers (adjusted for meat intake), and 2) the lower 33.3% (low meat; LM) vs. the upper 66.6% (high meat; HM) of the study sample with regard to red/processed meat intake (adjusted for fiber intake). In addition, a possible interaction between the lower 33.3% of the sample

with respect to red/processed meat intake and the upper 33.3% of the sample with regard to fiber intake will be examined using logistic regression with same covariates as stated above.

The result from the primary and key secondary outcomes will be presented in table 2, while other secondary outcomes will be presented in a separate table (Appendix table 1). Results from the secondary explorative analyses will be presented in table 3 and 4 in the Appendix.

### 6.3. Missing data

As previously stated (under section 4.3), the primary analyses will be based on the ITT population. Accordingly, participants will be followed up, assessed and analyzed as members of their initial dietary group, irrespective of their adherence to the planned course of treatment with biological agents and potential personal changes in dietary habits (i.e., independent of withdrawals and cross-over phenomena). Every effort will be made to minimize missing data (i.e. both baseline covariates [ $X$ 's] and outcome data [ $Y$ 's]). Loss to follow-up and missing data for various reasons is however difficult to avoid in pragmatic, real-world observational studies, from clinical practice.

We will apply the analysis framework suggested by White et al (2011) in which missing data related to the ITT approach depend on making plausible assumptions about the missingness of the data and including all participants in subsequent sensitivity analyses [24]:

**#1. Attempt to follow up all participants who signed informed consent**, even if they withdrew from allocated treatment or significantly modified their dietary habits (i.e., we contact all individuals unless they explicitly stated that they had withdrawn their consent).

**#2. Perform a main analysis of all observed data that are valid under a plausible assumption.** For our primary analyses we will assume that data is 'Missing At Random' (MAR). The MAR assumption requires that, conditional on the observed data for the case,  $Y_{obs}$ , the probability that a value is missing does not depend on the true values of the missing items,  $Y_{mis}$ . Multiple imputation (MI) will be used to account for participants from whom we have an answered FFQ (i.e. the ITT population) but potentially with missing outcome information at follow-up.

**#3. Perform sensitivity analyses.** In order to explore the effect of departures from the assumption made in the main analysis (#2) other analysis techniques will be applied; these models will potentially be informative even if data are 'Missing Not At Random' [MNAR].

**Use and reporting of analyses using multiple imputation.** When we assume data are missing at random (MAR), then unbiased and statistically more powerful analyses is possible by building a more general model based on multiple imputation. Multiple imputation (MI) is a general approach to the problem of missing data that allow for the uncertainty about the missing data by creating several different plausible imputed data sets and appropriately combining results obtained from each of them.

The MI first stage will be to create multiple (i.e. at least 5) copies of the dataset, with the missing values replaced by imputed values. These will be sampled from their predictive distribution based on the observed data.

The MI second stage will be to use standard statistical methods to fit the logistic regression model of interest to each of the imputed datasets; variables included in the imputation models will be listed. At least five imputed datasets will be created. Estimated associations (i.e.  $\ln[OR_i]$ ) in each of the imputed datasets will differ

because of the variation introduced in the imputation of the missing values, and they are only useful when averaged together to give overall estimated associations. Standard errors will be calculated using Rubin's rules [51] which take account of the variability in results between the imputed datasets, reflecting the uncertainty associated with the missing values. Valid inferences are obtained because we will be averaging over the distribution of the missing data given the observed data.

We will report the number of missing values for each variable of interest, and the number of cases with complete data for each important component of the analysis. We will provide reasons for missing values if possible and indicate how many individuals were excluded because of missing data when reporting the flow of participants through the study (Figure 1). We will provide explicit reasons for missing data for the primary outcome measure in terms of other variables and explore whether there are differences between individuals with complete and incomplete primary outcome data, by performing logistic regression analyses with "missingness" being the dependent variable ( $Y_{\text{Mis}}$  vs.  $Y_{\text{Obs}}$ ) and various baseline characteristics (covariates) as independent variables.

The selection of the variables to be used in the imputation of missing data will follow the following three basic rules, that will enable us to perform multiple imputation and analysis that is statistically robust:

1. Include all the key analysis variables, regardless of whether they have missing data;
2. Include other variables that are correlated or associated with the primary outcome we intend to analyze (regardless of whether these variables will ultimately be included in our analysis);
3. Include variables that predict item missing data on the analysis variables (again regardless of whether these variables will ultimately enter our analysis).

We will report the details of the software used and of key settings for the imputation modeling; incl. the number of imputed datasets that were created. We will use mainly default options but do specify a specific SEED value (e.g. the specific date of the analysis); this seed will be used to initiate the generation of random numbers that are used in the imputation process. The specification of a fixed SEED value enables us to exactly replicate the random number generation sequence and reproduce the results of a multiple imputation analysis run. We will use the following default settings: M=5 repetitions and 20 burn-in iterations.

Since our analytic objective is to estimate the Odds Ratios (from logistic regression) of clinical response depending on the dietary group (and other covariates simultaneously), we will use logistic regression with a "BY statement" to execute five separate logistic regressions, one for each imputation repetition data set contained in the corresponding "MI data set".

The MI third and final step in our analysis plan is to combine these five sets of regression estimates to produce the final MI estimates of the logistic regression model parameters, their standard errors, and 95% CIs for the true parameter values. As a consequence, the parameter estimates from the five individual logistic regressions are averaged and the associated standard errors account for the imputation variability.

